### **3.2.2 Secondary Outcome Measures**

Immune responses will be parameterized as the proportion of subjects with at least a four-fold rise after each dose from baseline or as the mean titer after each dose in any of the following:

- Serum hemagglutination inhibition (HAI) antibodies
- Serum neutralizing antibodies
- Serum immunoglobulin class A (IgA) or immunoglobulin class G (IgG) antibodies measured by enzyme-linked immunoassay (EIA)
- Mucosal IgA antibodies in nasal wick specimen

Virus shedding will be parameterized as the proportion of subjects shedding virus [detected by real-time reverse transcriptase polymerase chain reaction (rRT-PCR) in nasal or conjunctival swabs or by isolation in chicken embryos] at any time-point. Shedding data will be reported for every subject at every measured time-point. Molecular characterization of any isolated shed virus will be reported with sequence details of any loss of attenuation mutations.

### **3.2.3 Exploratory Outcome Measures**

Cellular immune responses (cytokine and T-cell) will also be measured using isolated peripheral blood mononuclear cells (PBMCs) tested by flow cytometry and/or enzyme-linked immunosorbent spot (ELISPOT) assay. These analyses will be exploratory and descriptive only.

## 4 Study Design

This is a phase I, double-blind, individually-randomized (3:1, vaccine:placebo), controlled trial with two groups, LAIV H7N3 and matched placebo. Healthy male and female adults 18 through 49 years of age will be invited to participate. For feasibility reasons and in order for an independent Safety Monitoring Committee (SMC) to review safety data in a small group of subjects initially, the total cohort of 40 subjects will be enrolled in two sub-cohorts: one cohort of 12 subjects, randomized at 3:1 (9 vaccine and 3 placebo), followed two weeks later by a second cohort of 28 subjects randomized at 3:1 (21 vaccine and 7 placebo). After all 12 volunteers of the first sub-cohort have been observed for the first isolation period (Day 1 to Day 7), an interim safety review will be performed by the SMC. The SMC will review all AEs, including clinical laboratory evaluations (pre- and post-vaccination) and shedding data, for all subjects and will advise if the volunteers of the first sub-cohort may receive dose two of study vaccine or placebo and if the additional 28 volunteers of the second sub-cohort may be enrolled into the study. As for the first sub-cohort, the SMC will also review all safety data for the second sub-cohort and for the entire participant population of the trial. For each sub-cohort, the procedures and timelines are here summarized.

On the day of first screening, about 7 days (between 4 and 14 days) prior to administration of dose one of study vaccine or placebo, subjects will be screened for eligibility through medical history review, physical examination, testing for serologic evidence of chronic viral infection [human immunodeficiency virus (HIV), hepatitis B virus (HBV) or hepatitis C virus (HCV), with proper pre- and post-test counseling], routine biochemical and hematological blood tests and urinalysis by dipstick.

Subject screening for eligibility will continue and be completed on the second screening day (S2). This second screening day will occur the same day as scheduled admission to the isolation unit and administration of study vaccine or placebo (Day 0). Women will undergo pregnancy tests using urine samples. All subjects will undergo an ear, nose and throat (ENT) examination. Fully eligible subjects will be admitted to the isolation unit. At that time, nasal swab, nasal wick, and blood specimens will be collected for virologic and immunological testing prior to administration of study vaccine or placebo. Blood and urine specimens will be again collected for routine biochemical and hematological blood tests and urinalysis by dipstick; these results will serve to define baseline status for subject prior to receipt of study vaccine or placebo but will not be used for screening purposes. Subjects will be unaware of which allocation, LAIV H7N3 or matched placebo, is received; study vaccine and placebo will be masked. Subjects will be carefully monitored for adverse reactions while in the isolation unit.

All subjects will remain in the isolation unit for at least 7 days after receipt of study vaccine or placebo. Nasal swabs will be collected daily while subjects are in isolation to test for presence of influenza virus shed in the nasal passage. Any subject exhibiting conjunctivitis will also have a conjunctival swab collected on the day of appearance of the sign. Any subject exhibiting influenza A virus shedding, as determined by real-time RT-PCR positivity on a nasal swab specimen, in the 2 days prior to each planned discharge day after each dose (Days 6 or 7 or Days 34 or 35) will be kept in the isolation until PCR-diagnosis results

confirm that no influenza virus is present in a tested clinical specimen for at least two consecutive days.

Any subject still exhibiting evidence of influenza virus shedding in a nasal swab on Days 6 or 7 or Days 34 or 35 post-administration with each dose might be placed on influenza antiviral (oseltamivir) treatment at the standard dose for treatment of 75 milligrams (mg) twice a day for a course of 5 days.

After discharge from the isolation unit, subjects will complete diary cards for AEs and use of concomitant medications. Subjects will return to the isolation unit at four weeks (Day 28) after administration of dose one of study vaccine or placebo. At that time, similar procedures will be used for admittance to the isolation unit, for receipt of dose two of study vaccine or placebo and for isolation and follow-up, with the additional procedure of review of interim histories (and diary cards) since first discharge after dose one.

After second discharge from the isolation unit, subjects will again complete diary cards for AEs and use of concomitant medications. Subjects will then return to the study center at four weeks (Day 56) after administration of dose two of study vaccine or placebo for their final study visit. Interim histories (and diary cards) will again be reviewed and final blood and nasal wick specimens will be collected. Women will also undergo a final pregnancy screen. Subjects will complete the study at this time.

For assessment of safety, subjects will be observed for two hours after each administration of study vaccine or placebo. Twice daily (early morning and late afternoon) examination will be also used to assess reactions for 7 days after each administration of study vaccine or placebo. ENT examination will also occur once per day on Days 7, 28, 35 and 56. Subjects will complete diary cards for unsolicited AEs from the day of each discharge until return to the isolation unit for dose two (at Day 28) or until return to the study center for the final study visit at four weeks post dose two (at Day 56). To assess safety, blood and urine specimens will also be collected on days 7, 28 (prior to administration of dose two of study vaccine or placebo), 35 and 56, for testing by routine biochemical and hematological blood tests and by urinalysis by dipstick.

For the evaluation of mucosal IgA antibody, nasal wick specimens will be collected on Day 0 (prior to administration of dose one of study vaccine or placebo), on Day 28 (prior to administration of dose two of study vaccine or placebo) and on Day 56. For the evaluation of serum antibodies (by HAI, microneutralization and IgA and IgG EIA), serum specimens will be collected on Day 0 (prior to administration of dose one of study vaccine or placebo), on Day 28 (prior to administration of dose two of study vaccine or placebo) and on Day 56. To study virus infectivity (by isolation in chicken embryos) and stability (by molecular sequencing of any isolated virus), nasal swab specimens will be taken on Days 1, 2, 3, 5, 7, 29, and 31. To assess priming and stimulation of cytotoxic T lymphocytes and other cytokine indicators, whole blood for isolation of PBMCs will be collected on Days 0 (prior to administration of dose one of study vaccine or placebo), on Day 28 (prior to administration of dose two of study vaccine or placebo) and on Day 56.

## 5 Study Enrollment and Withdrawal

Forty health male and female adult volunteers will be included in the full vaccine study. It is expected that up to 50 persons may need to be screened in order to confirm eligibility for 40 subjects.

### 5.1 Subject Inclusion Criteria

Questions about eligibility must be addressed prior to enrollment. The following criteria must be met before a subject may be enrolled for participation:

- Legal male or female adult 18 through 49 years of age at the enrollment visit.
- Literate and willing to provide written informed consent.
- Free of obvious health problems, as established by the medical history and screening evaluations, including physical examination.
- Capable and willing to complete diary cards and willing to return for all follow-up visits
- Willing to comply with the rules of the isolation unit (including willing and able to take oseltamivir influenza antiviral medication, should that be recommended by a study physician).
- For females, willing to take reliable birth control measures throughout the entire period of participation in the study.

### 5.2 Subject Exclusion Criteria

Subjects with any of the following conditions will be excluded from participation:

- Participation in another clinical trial involving any therapy within the previous three months or planned enrollment in such a trial during the period of this study.
- Receipt of any non-study vaccine within four weeks prior to enrollment or refusal to postpone receipt of such vaccines until four weeks after study completion.
- Practice of nasal irrigation on a regular basis within the past six months or has engaged in nasal irrigation within two weeks prior to enrollment.
- Recent history of frequent nose bleeds (>5 within the past year).
- Clinically relevant abnormal paranasal anatomy.
- Recent history (within the past month) of rhino or sinus surgery, or surgery for any traumatic injury of the nose.
- Current or recent (within two weeks of enrollment) acute respiratory illness with or without fever.
- Other acute illness at the time of study enrollment.

- 
- Receipt of immune globulin or other blood products within three months prior to study enrollment or planned receipt of such products during the period of subject participation in the study.
  - Chronic administration (defined as more than 14 consecutively-prescribed days) of immunosuppressants or other immune-modulating therapy within six months prior to study enrollment. (For corticosteroids, this means prednisone or equivalent,  $\geq 0.5$  mg per kg per day; topical steroids are allowed, exclusive of nasal.)
  - Participation in any previous trial of any H5 or H7 containing influenza vaccine.
  - History of asthma.
  - Hypersensitivity after previous administration of any influenza vaccine.
  - History of wheezing after past receipt of any live influenza vaccine.
  - Other AE following immunization, at least possibly related to previous receipt of any influenza vaccine.
  - Suspected or known hypersensitivity to any of the study vaccine components, including chicken or egg protein.
  - Seasonal (autumnal) hypersensitivity to the natural environment.
  - Acute or chronic clinically significant pulmonary, cardiovascular, hepatic, metabolic, neurologic, psychiatric or renal functional abnormality, as determined by medical history, physical examination or clinical laboratory screening tests, which in the opinion of the investigator, might interfere with the study objectives. Subjects with physical examination findings or clinical laboratory screening results which would be graded 2 or higher on the AE severity grading scale (see Attachments) will be excluded from entry into the study and will be excluded from receipt of dose two of study vaccine or placebo.
  - History of leukemia or any other blood or solid organ cancer.
  - History of thrombocytopenic purpura or known bleeding disorder.
  - History of seizures.
  - Known or suspected immunosuppressive or immunodeficient condition of any kind, including HIV infection.
  - Known chronic HBV or HCV infection.
  - Known tuberculosis infection or evidence of previous tuberculosis exposure.
  - History of chronic alcohol abuse and/or illegal drug use.
  - Claustrophobia or sociophobia.
  - Pregnancy or lactation. (A negative pregnancy test will be required before administration of study vaccine or placebo for all women of childbearing potential.)
  - Any condition that, in the opinion of the investigator, would increase the health risk to the subject if he/she participates in the study or would interfere with the evaluation of the study objectives.
-

## 5.3 Treatment Assignment Procedures

### 5.3.1 Randomization Procedures

This is a phase I, double-blind, individually-randomized (3:1, study vaccine:placebo), controlled trial with two groups, LAIV H7N3 and placebo. Forty healthy adults 18 through 49 years of age will be included in the trial. Study vaccine or placebo will be allocated to codes through the use of a computerized randomization scheme generator. A detailed *Randomization* standard operating procedure (SOP) will be developed prior to study initiation. Regardless of exact plan, an allocation code will be randomly assigned to each subject using a method which maintains the 3:1 ratio of study vaccine to placebo in each study sub-cohort.

### 5.3.2 Masking Procedures

Study vaccine and placebo will have similar formulations (LAIV H7N3 is a lyophilized formulation which must be reconstituted with sterile water for injections and placebo is the same lyophilized material without vaccine virus). However, because study vaccine and placebo will be clearly labeled as such, an unblinded study clinician will be assigned to prepare all study vaccine and placebo preparations. This study clinician will not administer the preparations and will not reveal to either other study staff or to the subject which preparation was given. Preparation of study vaccine or placebo and filling of spray dosing devices will be done by the unblinded clinician behind a screen. Filled devices will be carefully handed to the blinded study clinician administering the preparation. Preparation of study vaccine and placebo and filling of spray dosing devices will be closely monitored by an independent monitor from PATH Vaccine Solutions (PVS) and a Sponsor representative. Adherence to randomization will also be closely monitored to confirm that the randomization scheme is not broken. Study vaccine or placebo given to each individual subject will be documented on the CRF with the appropriate allocation code. Full details will be specified in a *Masking* SOP prior to trial initiation.

All blinded study staff will remain blinded throughout the trial. If any subject develops an SAE possibly related to receipt of study treatment, treatment allocation to the subject may be communicated to the investigator only if that information is deemed necessary to properly treat the subject for the SAE. In such cases, PVS must be consulted prior to any unblinding.

In order to maintain isolation unit staff blinding throughout the study, one designated investigator will receive all daily results of rRT-PCR testing. This investigator will maintain these results in a secure location and will not share results with other investigators or study staff. Likewise, laboratory personnel conducting the rRT-PCR testing will not share the results with others not designated to receive these results. Only in the event that a subject prematurely leaves the isolation unit for any reason may any subject's influenza A positivity be revealed. The designated person holding these results will not participate in study evaluations of safety. This designated person will be consulted on Day 7 and Day 35 in order to confirm that no subject has influenza A positivity in a nasal swab specimen collected in either of the final two days of planned stay in the isolation unit after each dose.

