Subject screening for eligibility will continue and be completed on the second screening day (S2). This second screening day will occur the same day as scheduled admission to the isolation unit and administration of study vaccine or placebo (Day 0). Women will undergo pregnancy tests using urine samples. All subjects will undergo an ear, nose and throat (ENT) examination. Fully eligible subjects will be admitted to the isolation unit. At that time, nasal swab, nasal wick, and blood specimens will be collected for virologic and immunological testing prior to administration of study vaccine or placebo. Blood and urine specimens will be again collected for routine biochemical and hematological blood tests and urinalysis by dipstick; these results will serve to define baseline status for subject prior to receipt of study vaccine or placebo but will not be used for screening purposes. Subjects and investigators conducting assessments of safety will be unaware of which allocation, LAIV H7N3 or matched placebo, is received; study vaccine and placebo will be masked. Subjects will be carefully monitored for adverse reactions while in the isolation unit.

All subjects will remain in the isolation unit for at least 7 days after receipt of study vaccine or placebo. Nasal swabs will be collected daily while subjects are in isolation to test for

**Description of Study  
Design, cont.:**

presence of influenza virus shed in the nasal passage. Any subject exhibiting conjunctivitis will also have a conjunctival swab collected on the day of appearance of the sign. Any subject exhibiting influenza A virus shedding, as determined by real-time RT-PCR positivity on a nasal swab specimen, in the 2 days prior to each planned discharge day after each dose (Days 6 or 7 or Days 34 or 35) will be kept in the isolation until PCR-diagnosis results confirm that no influenza virus is present in a tested clinical specimen for at least two consecutive days.

Any subject still exhibiting evidence of influenza virus shedding in a nasal swab on Days 6 or 7 or Days 34 or 35 post-administration with each dose might be placed on influenza antiviral (oseltamivir) treatment at the standard dose for treatment of 75 milligrams (mg) twice a day for a course of 5 days.

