#### **11.3.1 Safety**

The safety profile will be parameterized as the proportion of subjects experiencing adverse events (AEs) of the following four categories:

- Immediate reactions occurring within two hours of administration of any dose, measured as observed by study staff or reported by the subject to study staff.
- Adverse events commonly associated with intranasal vaccination (solicited local and systemic reactions) occurring greater than two hours after administration of any dose of study vaccine or placebo through 7 days following any dose, measured as observed by study staff or reported by the subject to study staff.
- All other adverse events (including unsolicited events) occurring during the 7 days following any dose, measured as observed by study staff or reported by the subject to study staff. This includes abnormal laboratory findings from blood and urine specimens collected on Days 7 and 35.
- All serious adverse events (SAEs) occurring within 4 weeks of receipt of any dose, as observed by study staff, reported by the subject to study staff, or noted by the subject on a diary card. This includes abnormal laboratory findings from blood and urine specimens collected on Days 28 (pre-vaccination) and 56.

Counts of all events will be reported and summarized according to event severity, as “any local AE”, or “any systemic AE”, and by relationship to administration of study vaccine or placebo, as deemed by a blinded study clinician. Percentages of subjects experiencing each reaction or event or at least one reaction or event will be calculated along with 95% confidence intervals (CIs) using exact statistical methods.

No multiplicity adjustment to the error rate, alpha, will be made because there are no statistical hypotheses and all analyses will be descriptive.

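### The masking section promises unbroken staff blinding and disclosure of PCR positivity only on premature exit, but retaining or treating late shedders lets staff infer it, so relationship calls for those subjects cannot be assumed blinded

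*Protocol*

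**What the plan says.** Section 5.3.2 (Masking Procedures) states that "All blinded study staff will remain blinded throughout the trial". To achieve this, one designated investigator, who takes no part in safety evaluation, holds all daily rRT-PCR results and shares them with no other investigator or staff member. The exception is worded exclusively: a subject's positivity may be disclosed "Only in the event that a subject prematurely leaves the isolation unit for any reason". Section 8.2.2.1 repeats the rule. Section 5.3.2 also provides that "This designated person will be consulted on Day 7 and Day 35", to confirm that nobody is positive before discharge. It does not say what is disclosed when somebody is.

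Other sections act on the same results:

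- The Protocol Summary and section 4 say that a subject positive in the last two planned days after either dose "will be kept in the isolation until PCR-diagnosis results confirm that no influenza virus is present in a tested clinical specimen" on two consecutive days.
- Sections 7.2.8 and 7.2.17 make discharge conditional on negative swabs on Days 6 and 7, or Days 34 and 35.
- The Trial Scheme footnotes and section 8.2.2.1 continue daily swabbing for subjects who stay.
- Section 4 and the Trial Scheme allow oseltamivir for these subjects only. Section 5.1 requires subjects to be willing to take it, "should that be recommended by a study physician".
- Section 9.2.3 names late shedding as the reason for a stay beyond seven days.

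Section 11.3.1 summarises events by severity and by relationship to study product, the latter "as deemed by a blinded study clinician".

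**The concern.** The protocol sequesters PCR results precisely because they could unblind staff. It then attaches two visible consequences to a positive result, a longer stay and possibly an antiviral, and describes nothing that would hide the reason. Staff in the unit can work out the result by a route that the exclusive wording in 5.3.2 does not allow. In a population described in section 2.2 as immunologically naive to H7N3, a late positive points towards vaccine.

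At stake is the credibility of the relationship table. If a clinician believes a subject received vaccine, later events may be attributed to it more readily, or less, and severity grading could shift too. This would fall mostly on one arm, in a trial whose comparison group is only 10 subjects. Nothing in the protocol separates the assessing clinician from staff who see the retention, and no time is set by which a relationship call must be fixed.

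**Working it through.** The protocol states no figure to reproduce here. The check is a comparison of texts, followed by an illustration of size.

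**1. Do the texts agree?**

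| Statement | Where | Consequence |
|---|---|---|
| Staff stay blinded; positivity disclosed only on premature exit | 5.3.2, 8.2.2.1 | No other route to knowledge is permitted |
| Positive on Days 6/7 or 34/35 means kept in the unit | Summary, 4, 7.2.8, 7.2.17, 8.2.2.1 | Stay beyond Day 7/35 signals positivity |
| Oseltamivir possible for the same subjects only | Summary, 4, Trial Scheme | Treatment signals positivity |
| Late shedding named as reason for a longer stay | 9.2.3 | The reason is known to anyone applying the SAE definition |

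They do not agree. A retained subject has not left early, so the exception in 5.3.2 does not apply, yet positivity becomes inferable.

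**2. How strongly does retention point to vaccine?** Allocation from section 4: 9 + 21 = 30 vaccine and 3 + 7 = 10 placebo, so the prior probability of vaccine is 30/40 = 0.75. Let s and f be the late-positive rates on vaccine and placebo. Neither is in the protocol; both are assumptions. Then

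P(vaccine | retained) = 0.75s / (0.75s + 0.25f).

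- s = 5%, f = 1%: 0.0375 / (0.0375 + 0.0025) = 0.94
- s = 5%, f = 2%: 0.0375 / (0.0375 + 0.0050) = 0.88
- s = 20%, f = 1%: 0.1500 / (0.1500 + 0.0025) = 0.98
- s = f: 0.75, so retention then tells nothing

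Discharge on time tells little: with f = 1%, P(vaccine | discharged) is 0.74 at s = 5% and 0.71 at s = 20%.

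**3. How many subjects?** The expected number of late-shedding vaccinees per dose is 30s; the chance of at least one is 1 − (1 − s)^30.

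| Assumed s | Expected | Chance of at least one |
|---|---|---|
| 1% | 0.3 | 1 − 0.99^30 = 26% |
| 5% | 1.5 | 1 − 0.95^30 = 79% |
| 30% | 9 | 1 − 0.70^30, nearly 100% |

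**4. Which assessments are exposed?** Three of the four primary categories in 11.3.1 close seven days after each dose. Retention is decided on Day 7 or Day 35, so nearly all of the first window is assessed before anything can be inferred. What remains is:

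- all dose-two assessments of subjects retained after dose one;
- events assessed during a prolonged stay or later follow-up, including SAEs;
- Day 7 and Day 35 laboratory AEs whose results arrive after the consultation.

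**The case against.** The strongest reply is that this is a conflict of wording with little statistical consequence, and several parts of that reply stand.

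- A reader might infer that the primary safety result itself loses its blinding. The documents do not support this. The four primary categories count events regardless of relationship, and section 9.2.2 says that the relationship judgement does not determine what is recorded. Relationship is one descriptive breakdown, and section 11.1 sets no hypotheses.
- A reader might also infer that retention discloses the allocation. It does not. The discharge test is for influenza A, subtype confirmation follows within 72 hours (8.2.2.1), and section 2.3.1.1 accepts that a shedder could infect placebo recipients. Retention supports a strong inference only.
- Section 5.1 does not say that the physician recommending the antiviral also assesses adverse events; that person could be the designated results holder. The firm route is that unit staff see who stays.
- Section 2.1 reports that comparable avian live vaccines on another donor strain replicated poorly in seronegative adults, so low late-shedding rates are plausible. This is why 1% is included in the range.

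The reply fails on one point. Section 5.3.2 defers detail to a Masking SOP, but an SOP cannot make the exclusive disclosure sentence compatible with PCR-driven retention. The protocol text has to change.

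**Conclusion.** The contradiction is certain and does not depend on any rate: blinding throughout is a stated property that the design does not have for late shedders. The description of relationship calls as blinded is therefore not assured for subjects retained or treated after dose one, chiefly in their dose-two assessments, nor for events assessed in either dose's prolonged stay or later follow-up. The damage is limited to the relationship tabulation and possibly severity grading.

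The number affected is unknown. On assumed late-shedding rates of 1% to 30%, it ranges from probably nobody to about nine vaccinees per dose. The link from retention to vaccine rests on the further assumption that placebo recipients are late-positive less often than vaccinees. The correction is cheap and should be made.

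**What to change.** Leave the containment and treatment rules as they are and change three things.

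1. Reconcile 5.3.2 and 8.2.2.1 with the retention provisions: state that positivity becomes known or inferable to named roles when a subject is retained or offered the antiviral, and qualify the promise of blinding throughout accordingly.
2. Require severity and relationship entries for events known by then to be signed before the designated investigator is consulted on Day 7 and Day 35. The 16:00 time in 7.2.8 and 7.2.17 is when results reach that investigator, not a release time, so the sign-off should be tied to the consultation.
3. In 11.3.1, flag relationship and severity calls made after retention or antiviral use. This includes all dose-two calls for subjects retained after dose one and laboratory AEs reported after the consultation. Show the relationship table with and without flagged calls, and do not describe flagged calls as blinded.

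Sign-off cannot restore blinding for dose-two calls in subjects already retained after dose one; only the flag deals with those. The cost is sign-off work on the two discharge days and one extra flag in the data and tables. No additional assessors are needed.
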